##### Movement parameters (assessed at T0 and T2)

All movement assessments will be performed at the corresponding 3D motion laboratories of the consortium using the same standardized acquisition protocol and optoelectronic system. Within a total estimated time < 45 min, all children will undergo UE analyses. In addition, the children with independent walking or necessitating minimum assistance, will also undergo LE analyses. We expect to accomplish a 60% of entire acquisitions based on the Brest team expertise and recent evidence on 10-month old infants [57].

To assess UE 3D motion analyses, an adapted version of previous procedures [58] will be used as protocol. Anatomical landmarks on upper limb will include markers on the thorax, acromion, arm, forearm, hand and fingers. For the tasks, children will be positioned in a standardized chair facing a Table. A total of three different reach-to-grasp tasks will be presented. The Arm Profile Score [59] will be used to assessed kinematic and spatiotemporal parameters. In addition, electromyographic signals in four muscles (long head of the triceps brachii, short head of the biceps brachii, pronator teres and quadratus) will be analyzed following Sarcher et al. methods [60] as well as guidelines of the European project “Surface Electromyography for the Non-Invasive Assessment of Muscles”(SENIAM) [61]. The EMG-Profile Score for UE motion [62] will be used to assessed muscle activation indices.

To assess gait 3D motion, sixteen anatomical landmarks will be highlighted with reflective markers following Davis’ protocol [63]. Barefoot, children will be asked to walk unassisted or with minimum assistance down a 10-m-long path, registering a minimum of ten trials. Kinematic and spatio-temporal parameters will be analyzed. In addition, electromyographic signals in five muscles (rectus femoris, vastus lateralis, medial hamstrings, tibialis anterior and gastrocnemius-soleus) will be analyzed using a 16-channel electromyography system following the SENIAM guidelines [61].

To assess global physical activity, wrist sensors [64, 65] will be used to measure active and resting states, including periods of intensity, posture and gait using bar-code parameters. Wrist sensors have the advantage of having automatic calibration and simple positioning. Total time spent in movement (measured in percentage), such as crawling, walking or running during either the HABIT-ILE or the control period, will be considered as the main outcome.

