*Hypothesis: Advanced brain imaging techniques will show greater changes in grey and white matter, and in connectivity for the e-HABIT-ILE group compare to the control group.*
Aim: To establish the e-HABIT-ILE effectiveness in generating movement characteristics’ changes on upper and lower extremities.

*Hypothesis: Greater improvements in kinematic parameters for upper and lower extremities movements will obtained the e-HABIT-ILE group compared to the control group.*

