### Statistical analysis

Primary outcome changes (GMFM-66) will be assessed using analysis of covariance (ANCOVA) between groups, including adjustment for baseline measurements following Vickers’s recomendations [66]. Secondary outcomes changes will be also analyzed with ANCOVA measurements (or non-parametric equivalent when normality and homoscedasticity are not met). For exploratory reasons, other subgroup characteristics (such as age) will also be analyzed.

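### Motion analysis is expected to be only 60% complete, yet kinematic change is analysed by ANCOVA, which without imputation uses only children measured at both T0 and T2

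*Protocol article*

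**What the plan says.** In the protocol article, Movement parameters are scheduled at T0 and T2 only. On who is measured, the section says that "all children will undergo UE analyses" and that "the children with independent walking or necessitating minimum assistance, will also undergo LE analyses"; the number of such walkers is not given. On expected yield it says: "We expect to accomplish a 60% of entire acquisitions". It does not say whether the 60% refers to visits, to children over both visits, or to the full set of upper-limb, gait and EMG recordings.

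Under Statistical analysis, the method is "Secondary outcomes changes will be also analyzed with ANCOVA measurements", with a non-parametric alternative if assumptions fail. Baseline adjustment is spelled out for GMFM-66 and reaches the other outcomes only by implication.

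The hypothesis under Secondary aims is worded for the randomised groups: "Greater improvements in kinematic parameters for upper and lower extremities movements will obtained the e-HABIT-ILE group", compared with control.

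**The concern.** The article forecasts substantial missing motion data and then fixes, for all secondary outcomes, a method that copes poorly with it. A change score needs both visits whether or not baseline is also a covariate. So, unless values are imputed, a child with one usable visit adds nothing to the kinematic comparison.

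Two things are at stake. One is avoidable loss of precision in the biomechanical domain, which is one of the three that the trial sets out to assess. The other is interpretation: the comparison rests on children able to cooperate with the procedure, while the hypothesis speaks of the groups as a whole.

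**Working it through.** **The plan's own sample size, to see what it covers.** Inputs from Sample size: difference 5 logits, SD 5 logits, α 0.05 (taken as two-sided), power 0.90. The normal approximation gives 2 × (1.960 + 1.282)² × (5/5)² = 21.0, so 22 per arm. The t-test gives 23 per arm (power 0.912), as stated. The step from 46 to 50 allows for 1 − 46/50 = 8% loss. All of this concerns GMFM-66; no sample size or power is given for kinematics.

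**Children with both visits, out of 50.**
- 60% of children complete at both visits, or exactly the same children succeeding twice: 0.60 × 50 = 30 (15 per arm).
- 60% at each visit, independent between visits: 0.60² × 50 = 18 (9 per arm).
- 60% at each visit with the least possible overlap: (0.60 + 0.60 − 1) × 50 = 10. This is a bound, not a plausible case.
- 60% complete on the whole battery: for a single parameter the number can exceed 30, because a child with valid reach-to-grasp data but failed gait or EMG recordings still enters the upper-limb analysis.

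Gait analysis starts from fewer than 50 if any child does not walk; how many is not stated.

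**Effect on precision, without assuming an effect size.** The standard error scales as 1/√n. Against 25 per arm it is √(25/15) = 1.29 times larger with 15 per arm and √(25/9) = 1.67 times larger with 9.

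**What a joint T0/T2 model recovers.** Assume unit variance at both visits, correlation ρ between T0 and T2, data missing completely at random, balanced arms and known covariance. Let b be the number per arm with both visits and t the number with T2 only.
- Complete-pair ANCOVA: variance of the treatment effect = 2(1 − ρ²)/b.
- Constrained longitudinal model with common baseline mean: variance = 2/[b/(1 − ρ²) + t].
- Ratio of the first to the second = 1 + (t/b)(1 − ρ²).
- Reduction in standard error = 1 − 1/√ratio.

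Example: independent visits, b = 9, t = 6, ρ = 0.5. The variances are 2 × 0.75/9 = 0.1667 and 2/(12 + 6) = 0.1111, a ratio of 1.50 and an SE reduction of 18%.

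With 60% usable at each visit, 25 per arm, and ρ of 0.5 to 0.8 (assumed):

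| Share with both visits / T2 only | b, t per arm | Ratio at ρ = 0.5 | Ratio at ρ = 0.8 | SE reduction |
|---|---|---|---|---|
| 36% / 24% (independent) | 9, 6 | 1.50 | 1.24 | 18% to 10% |
| 45% / 15% | 11.25, 3.75 | 1.25 | 1.12 | 11% to 6% |
| 55% / 5% | 13.75, 1.25 | 1.07 | 1.03 | 3% to 2% |
| 60% / 0% (same children) | 15, 0 | 1.00 | 1.00 | 0% |

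In this balanced approximation the gain comes from children with T2 only; those with T0 only add nothing to the treatment contrast.

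**Finite-sample check.** Simulation with the covariance estimated (200 runs per setting, so approximate) gave SE reductions of about 9-26%, 6-12% and 2-5% in the first three rows. The order of the settings is the same. The upper end exceeds the formula partly because ANCOVA is itself less efficient with about nine pairs per arm.

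**The case against.** The strongest reply is that the article contradicts nothing. It gives a candid feasibility figure and a short statistical section. It does not say complete cases only, and ANCOVA is compatible with multiple imputation. Rules for partial recordings usually belong in a full protocol or SAP, which are not shown. This stands, and it is why the point is conditional on no imputation and is not a complaint that missing-data rules are absent.

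A reader might go further in several directions that the documents do not support:
- That at least 40% of children are lost. The unit of the 60% is undefined; if it means the whole battery, loss for one parameter can be smaller. The children concerned also stay in the trial and lack only kinematic data.
- That usable single-visit or partial data will be discarded. This would follow from the named method applied without imputation; it is not a stated rule.
- That kinematic power falls from 93% (25 per arm) to 75% (15) or 51% (9). Those figures need the standardised effect of 1.0 taken from GMFM-66, which says nothing about kinematics.
- That the gain from a joint model is large. Cooperation is probably a fairly stable trait of the child, so success at the two visits is likely to coincide and the gain would lie toward the lower end of the range.
- That a joint model removes the selection. It adds nothing for children who succeed at neither visit.

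It is also fair that a normal-theory mixed model in a small sample does not replace the non-parametric alternative that the article allows. That alternative should be kept.

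**Conclusion.** The point holds in a limited form. The article expects incomplete motion data and names, for outcomes measured at two visits, a method that without imputation uses only children with both. This could leave about 18 to 30 of 50 children for a kinematic comparison, or more for a single parameter if the 60% describes the full battery.

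A joint T0/T2 model would reduce the standard error by roughly 2-26%, and by nothing if the same children succeed at both visits. This rests on 60% usable per visit, T0-T2 correlations of about 0.5 to 0.8 and data missing at random, none of which the article establishes. The point touches secondary outcomes only; the GMFM-66 analysis and the sample size are unaffected.

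**What to change.** - State what the 60% counts: visits, children over both visits, or the whole recording set.
- For kinematic and EMG outcomes, replace complete-pair ANCOVA with a constrained longitudinal model: T0 and T2 both as responses, a baseline mean common to both arms, one treatment effect at T2, fitted by REML with a small-sample correction. Children with one usable visit then enter the model.
- Keep a non-parametric sensitivity analysis where normality fails.
- Analyse each task and parameter from whatever is validly recorded, and report usable acquisitions by arm and visit.
- Limit the kinematic conclusion to children able to complete an acquisition.

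The cost is analysis-plan wording and slightly more modelling; no extra children, visits or data are needed. The model assumes that missingness is explained by the observed data, and selection by ability to cooperate remains, which is why the conclusion needs the narrower wording.

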### Statistical analysis

Primary outcome changes (GMFM-66) will be assessed using analysis of covariance (ANCOVA) between groups, including adjustment for baseline measurements following Vickers’s recomendations [66]. Secondary outcomes changes will be also analyzed with ANCOVA measurements (or non-parametric equivalent when normality and homoscedasticity are not met). For exploratory reasons, other subgroup characteristics (such as age) will also be analyzed.

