### Study design

We will implement a multi-center RCT in three European countries: Belgium (Brussels), Italy (Pisa) and France (Brest and Angers). The study will compare the effect of two weeks of e-HABIT-ILE to that of usual motor activity, including usual rehabilitation. Children will be assessed at 3 period times: baseline (T0), two weeks after baseline (T1) and 3 months after baseline (T2). CONSORT guidelines will be followed when reporting this RCT (See Fig. 1).

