### Randomization process

Using a blind centralized electronic distribution system, children will be assigned either to a control or a treatment group. Before the first assessment and collection of informed consent, children will be paired regarding age at inclusion (1/2/3/4 years), etiology of CP (brain malformation/grey matter injury/periventricular white matter injury),

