### Sample size

The sample size calculation was based on the mean improvement in the GMFM-66 in the study by Bleyenheuft et al. (2017) [29]. In that study of school-aged children, the GMFM-66 increased by 7 logits in the intervention group and by 2 logits in the control group. The duration of the intervention (2 weeks) and the follow up period (3 months) were the same as in the present study. Considering the differences between the samples and the potential variability of our target population (pre-school children), we estimate that the standard deviation of change could reach a maximum of 5 logits. We thus hypothesized that there would be a minimum difference of 5 logits between groups, with a standard deviation of 5 logits, an α of 0.05 and a 1-β of 0.9. Consequently, 23 participants are needed per group (total of 46). Considering potential drop-outs, 50 participants will be included.

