### Outcomes

#### Primary outcomes

The primary outcome measure will be the difference between groups (e-HABIT-ILE and control) for changes in scores (T2-T0) in Gross Motor Function Measure (GMFM–66, measured in % of logits) [35]. This tool evaluates changes in gross motor function over time or following an intervention in children with CP using Rasch analysis. The items cover a large spectrum of activities ranging from lying and rolling to walking, running and jumping. Its responsiveness [36], reliability and validity have been demonstrated in children with CP [37, 38] including infants and toddlers [39].

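### The stated primary ANCOVA omits age and etiology, on which children are paired before allocation; if these factors are prognostic, its standard error is too large and the test is conservative.

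*Protocol article*

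**What the plan says.** **Allocation.** The Randomization process section describes a central electronic system that assigns children to one of two groups, and says "children will be paired regarding age at inclusion (1/2/3/4 years), etiology of CP (brain malformation/grey matter injury/periventricular white matter injury". The sentence breaks off after etiology, so further factors may exist. It is also not clear whether matched pairs, stratification or minimisation is meant.

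**Analysis.** The Statistical analysis section says "Primary outcome changes (GMFM-66) will be assessed using analysis of covariance (ANCOVA) between groups, including adjustment for baseline measurements". It names no pair, age or etiology term. The same paragraph adds "For exploratory reasons, other subgroup characteristics (such as age) will also be analyzed", which is the only analytic role that the article gives to age.

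**Endpoint and planning.** The Primary outcomes section defines the comparison as the "difference between groups (e-HABIT-ILE and control) for changes in scores (T2-T0) in Gross Motor Function Measure". The Sample size section assumes a "minimum difference of 5 logits between groups, with a standard deviation of 5 logits, an α of 0.05 and a 1-β of 0.9" and concludes that "23 participants are needed per group (total of 46") before an allowance for drop-outs.

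**The concern.** Choosing age and etiology as pairing factors implies that the authors expect them to predict outcome. Making the arms alike on such factors lowers the true sampling variance of the arm difference. The standard error printed by the ANCOVA reflects this only if the factors, or the pairs, are in the model. Otherwise their variance sits in the residual as if it were noise.

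At stake is the calibration of the confidence interval and p-value for the single primary comparison. The interval would be wider than it needs to be and the test would reject less often than its nominal level. Part of the precision that the allocation scheme provides would not reach the reported inference.

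**Working it through.** **1. The plan's own figure.** Inputs from the Sample size section: difference 5, SD 5, α 0.05 (taken as two-sided), power 0.90. The normal approximation is n = 2(1.96 + 1.2816)² × (5/5)² = 21.01, so 22 per group. The exact two-sample t-test gives power 0.8997 at 22 and 0.9125 at 23, so 23 is the smallest n that reaches 0.90. The stated 23 per group reproduces as an unpaired two-group calculation. Neither the planning nor the stated model uses the pairing.

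**2. Standard errors.** Let R² be the share of variance in GMFM-66 change, after baseline adjustment, that the pairing factors explain. If pairs match fully on those factors, R² is also the within-pair residual correlation. The SD of 5 is treated as the SD left after baseline adjustment. The protocol gives no value for R², so a range that includes 0 is shown.

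- Model-based SE, factors omitted: 5 × √(2/23) = 1.474 at every R².
- True SE under the pairing: 5 × √(2(1 − R²)/23).
- Excess of the first over the second: 1/√(1 − R²) − 1.
- Approximate type I error: 2[1 − Φ(1.96/√(1 − R²))].

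| R² (assumed) | True SE | SE too large by | Type I error, formula | Type I error, simulated |
|---|---|---|---|---|
| 0 | 1.474 | 0% | 0.050 | 0.048 |
| 0.1 | 1.399 | 5% | 0.039 | 0.036 |
| 0.2 | 1.319 | 12% | 0.028 | 0.028 |
| 0.3 | 1.234 | 20% | 0.019 | 0.020 |

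The last column simulates the baseline-only ANCOVA on 23 pairs with SD 5. Adding age and etiology brought the type I error back to about 0.05.

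**3. Power, with and without the allocation factors** (same simulation; pairing present in both models):

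| R² (assumed) | Difference 5: baseline only | Difference 5: + age, etiology | Difference 3: baseline only | Difference 3: + age, etiology |
|---|---|---|---|---|
| 0 | 0.91 | 0.91 | 0.51 | 0.51 |
| 0.1 | 0.92 | 0.93 | 0.51 | 0.55 |
| 0.2 | 0.93 | 0.95 | 0.51 | 0.59 |
| 0.3 | 0.94 | 0.97 | 0.51 | 0.65 |

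The baseline-only column at a difference of 5 rises with R² because the balance is working even when the model ignores it. The gain from adjustment there is therefore 0 to 3 points. It is larger, 0 to 14 points, at a difference of 3. That difference is not a planning value and is shown only for sensitivity.

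**4. Cost in degrees of freedom.** With 46 children, intercept, arm and baseline leave 46 − 3 = 43. Age as a continuous term (1) and etiology with three classes (2) leave 40. At R² = 0 the exact power at a difference of 5 changes from 0.912 on 43 df to 0.911 on 40 df.

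**The case against.** **The covariate list may be longer than the article shows.** The wording about baseline adjustment is inclusive, the article condenses a fuller document, and a sentence on exploratory subgroups does not bar age from the primary model. It is true that there is no outright contradiction. But the article states its primary model with one named covariate and gives an allocation factor a place elsewhere. The point concerns what is stated, not a detail left out, and it is best settled before outcome data are seen.

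**The size is unknown.** This stands. Baseline GMFM-66 may already carry much of what age would explain, and at R² = 0 nothing is wrong with the standard error. For the same reason, a reader should not infer that the standard error is too large whatever the data; that holds only if the factors are prognostic beyond baseline.

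**The consequence is mild.** This also stands. A reader might infer that the pairing is wasted, that false positives become more likely or that the trial is underpowered. The documents support none of these. The balance and the lower true variance remain, the type I error falls rather than rises, and power at the planned difference stays at about 0.91 or more without adjustment.

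**Adding site would cost power.** A reader might also think that a four-site trial must adjust for site. The text shown does not make site an allocation factor, so it is not part of this mismatch. With site terms added to age and etiology, simulated power at a difference of 5 and R² = 0 was 0.88 against 0.91 unadjusted. That cost comes from the site terms, not from age and etiology.

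**Conclusion.** The concern holds in a conditional form. As written, the primary model leaves out the factors on which allocation is balanced. If they explain 10% to 30% of the variance left after baseline (an assumption), the standard error is 5% to 20% too large and the two-sided type I error is about 4% to 2% instead of 5%. If they explain none, there is no effect.

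The direction is the same whether the scheme is matched pairs, stratification or minimisation, provided that it achieves balance. The sizes assume complete matching on the named factors, 23 per group and SD 5; looser matching would make them smaller. This is a mismatch in efficiency and calibration that is worth correcting because the correction is nearly free. It does not bias the estimate or invalidate the planned sample size.

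**What to change.** In the Statistical analysis section, state that the primary ANCOVA of GMFM-66 change (T2−T0) includes arm, baseline GMFM-66, age at inclusion, etiology and any other factor actually used in allocation. Use the same allocation factors, with the matching baseline score, in the secondary ANCOVAs. Add site only if it constrained allocation. Complete the description of the allocation factors in the Randomization process section so that the two lists can be matched.

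Adjusting for the factors, not for pair identifiers, keeps in the analysis any child whose pair partner drops out. The cost is one sentence and about 3 degrees of freedom. No new data are needed, because age and etiology are already recorded for allocation, and the loss of power is negligible if the factors turn out not to be prognostic.

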## Discussion

This protocol targets pre-school age children with bilateral CP which is the most prevalent topographic presentation of CP. In addition, the evidence about the effective therapies for this population is very limited. For this reason, we expect that if e-HABIT-ILE show important improvements in the different outcomes (functional, neuroplastic and biomechanical), we could impact on each child’s developmental curve, which would in turn impact the three domains of the International Classification of Functioning, Disability and Health for Children and Youth [67] at a short, mid- and long-terms.

All results emanating from this project will be published in peer-reviewed publications as well as international and local conventions. We expect an international impact in case of positive outcomes and effectiveness of e-HABIT-ILE, possibly changing the vision of these children’s care and, moreover, decreasing the economic load on the health system regarding this population.

## Data Availability

Not Applicable.

## Abbreviations

BOHA: Both Hands Assessment
ANCOVA: Analysis of covariance
CIMT: Constraint-induced movement therapy
COPM: Canadian Occupational Performance Measure
CP: Cerebral Palsy
DMC: Data Monitoring Committee
GMFM-66: Gross Motor Function Measure
HABIT-ILE: Hand-arm Bimanual Intensive Therapy Including Lower Extremities
LE: Lower Extremities
MA2: Melbourne Assessment-2
MPOC-20: Measure of the Process of Care
PEDI: Pediatric Evaluation of Disability Inventory
RCT: Randomized controlled trials
UE: Upper Extremities
YC-PEM: Young Children’s Participation and Environment Measure
